### 2.8. Primary Outcomes

State–Trait Inventory for Cognitive and Somatic Anxiety (STICSA): The STICSA is a 21-item self-report scale that assesses cognitive and somatic components of anxiety [66]. The STICSA comprises a state scale that measures individuals’ current anxiety symptoms and a trait scale that assesses one’s proneness to anxiety, more generally. In the present study, only the trait scale of the STICSA will be used. Items are scored on a 4-point scale ranging from 1 (‘not at all’) to 4 (‘very much so’). The STICSA has demonstrated excellent validity and reliability [67]. A cut-off score of 43 or higher on the STICSA has been suggested for detecting a probable anxiety disorder [68]. The STICSA has been validated for use in clinical samples of adults with anxiety disorders [67]. Although not explicitly validated in perinatal samples, it has been used in treatment studies with perinatal populations [69,70].

### 2.9. Secondary Outcomes

Generalized Anxiety Disorder 7-Item Scale (GAD-7): The GAD-7 is a 7-item self-report measure that assesses anxiety symptom severity over the previous two-week period [71]. Items are measured on a 4-point scale ranging from 0 (‘not at all’) to 3 (‘nearly every day’). A cut-off score of 10 or higher with a sensitivity of 89% and specificity of 82% has been suggested for detecting a probable diagnosis of Generalized Anxiety Disorder [71]. The GAD-7 has also been validated for use in perinatal samples [72].

Penn State Worry Questionnaire (PSWQ): The PSWQ is a 16-item self-report measure that assesses the tendency to worry [73]. Items are scored on a 5-point scale ranging from 1 (‘not typical at all’) to 5 (‘very typical’), with higher scores reflecting greater pathological worry. A cut-off score of 62 or higher has been suggested for determining a probable GAD diagnosis [74]. The PSWQ has demonstrated excellent internal consistency and validity across various populations and has been validated for use in perinatal samples [75].

Difficulties in Emotion Regulation Scale (DERS): The DERS is a 36-item self-report scale designed to assess difficulties with emotion regulation [76]. The DERS contains six subscales that measure the following: non-acceptance goals, impulse, awareness, strategies, and clarity. Items are rated on a 5-point Likert scale, ranging from 1 (almost never, 0–10%) to 5 (almost always, 91–100%), with higher scores reflecting greater difficulties regulating emotions. The DERS has demonstrated good internal consistency (α = 0.86) and test–retest reliability (0.74) and has been validated for use in perinatal samples [77].

Multidimensional Assessment of Interoceptive Awareness 2 (MAIA-2): The MAIA-2 is a 37-item self-report scale that assesses multiple dimensions of interoception (i.e., awareness of bodily sensations) [78]. Items are scored on a 6-point scale ranging from 0 (never) to 5 (always), with higher scores equating to more awareness of bodily sensation. The MAIA-2 has 8 subscales assessing dimension of noticing, not-distracting, not-worrying, attention regulation, emotional awareness, self-regulation, body listening, and trust. The MAIA-2 has been validated for use in a variety of clinical and non-clinical samples [79,80], although not explicitly in perinatal samples. Although the MAIA-2 has not been explicitly validated in perinatal samples, it is included here as a theoretically relevant measure of interoceptive awareness; findings will be interpreted cautiously, and formal psychometric evaluation in postpartum populations is planned for a future large-scale trial.

Interoceptive Sensitivity and Attention Questionnaire (ISAQ): The ISAQ is a 17-item self-report measure assessing sensitivity and attention to interoceptive signals [81]. Items are scored on a 5-point scale ranging from 1 (strongly disagree) to 5 (strongly agree), with higher scores indicating greater interoceptive sensibility. The ISAQ has 3 subscales assessing sensitivity to neutral bodily sensations, attention to unpleasant bodily sensations, and difficulty disengaging from unpleasant bodily sensations. The ISAQ has been validated for use in a variety of clinical and non-clinical samples, although not explicitly in perinatal samples [81]. Given the absence of explicit validation in perinatal samples, ISAQ findings will be interpreted cautiously, and future studies will examine its psychometric performance and construct validity in postpartum populations.

Five-Facet Mindfulness Questionnaire Short Form (FFMQ-SF): The FFMQ-SF is a 24-item self-report scale that assesses mindfulness [82]. Items are scored on a 5-point scale ranging from 1 (never or very rarely true) to 5 (very often or always true), with higher scores indicating greater mindfulness. The FFMQ-SF assesses five aspects of mindfulness, including observing, describing, acting with awareness, non-judging, and non-reactivity. The FFMQ-SF has been validated for use in a variety of clinical and non-clinical samples, although not explicitly in perinatal samples [82,83].

Edinburgh Postnatal Depression Scale (EPDS): The EPDS is a 10-item self-report measure that assesses symptoms of depression during the perinatal period [84]. Items are scored on a 4-point scale ranging from 0 to 3, with higher scores reflecting greater depressive symptomatology. The EPDS has demonstrated good sensitivity and specificity for a diagnosis of Major Depressive Disorder (MDD). A cut-off score of 13 or higher has been suggested for detecting a probable diagnosis of MDD during the postpartum period [85]. Additionally, the EPDS has also been used to assess postpartum anxiety, with 3 of the 10 included questions specifically probing into anxiety symptoms (EPDS-3A) [86].

Perceived Stress Scale (PSS): The PSS is the most widely used psychological instrument for measuring the perception of stress [87]. The PSS is a 10-item self-report measure designed to assess the degree to which situations in one’s life are appraised as stressful [88]. Items are scored on a 5-point scale ranging from 0 (‘never) to 4 (‘fairly often’) with higher scores reflecting greater perceived stress. The PSS has demonstrated good psychometric properties [87].

Social Provisions Scale (SPS): The SPS is a 24-item self-report scale that assesses perceived social support received within social relationships [89]. Items are scored on a 4-point scale ranging from 1 (strongly disagree) to 4 (strongly agree), with higher scores indicating higher levels of perceived social support [89]. The SPS has 6 subscales assessing dimensions of attachment, social integration, reassurance of worth, guidance, nurturance, and reliance. The reliability of the subscales is adequate (alpha ranging from 0.65 to 0.76).

Postpartum Bonding Questionnaire (PBQ): The PBQ is a 25-item self-report measure that assesses maternal–infant relations [90]. Items are scored on a 6-point scale ranging from 0 to 5 [90]. The PBQ has 4 subscales, including bonding, rejection, and anger towards the infant, infant-focused anxiety, and incipient abuse. The PBQ has good sensitivity, particularly for the bonding subscale (0.82) and the rejection and anger towards the infant subscale (0.88).

The Dyadic Adjustment Scale (DAS): The DAS is a 32-item scale used to measure an individual’s feelings about their relationship with an intimate partner [91]. The items are scored on 2-, 5-, 6-, or 7-point scales, with higher scores indicating greater relationship satisfaction. The DAS contains four subscales, including dyadic consensus, dyadic satisfaction, dyadic cohesion, and affective expression. The DAS has good internal consistency (alpha = 0.80).

World Health Organization Quality of Life Scale (WHOQoL): The WHOQoL-BREF is a 26-item self-report measure that assesses quality of life across four domains, including physical health, psychological health, social relationships, and environment [92]. Items are scored on a 5-point Likert scale ranging from 1 to 5, with higher scores indicating greater quality of life. The WHOQoL-BREF has demonstrated good discriminant validity, content validity, internal consistency, and test–retest reliability [92].

### 2.10. Exploratory Outcome

Resting-state Functional Connectivity: MRI data will be acquired using a 3T Discovery MR750 scanner (manufacturer: GE HealthCare; Chicago, IL, USA). Experimental group participants will undergo a 10 min anatomical MRI, followed by a 10 min resting-state fMRI during which they will be instructed to fixate on a cross. Changes in resting-state functional connectivity within the DMN and SN will be evaluated to examine whether improvements in self-reported anxiety, emotion regulation, and interoception are associated with neurobiological changes.

### 2.11. Data Management

Data collection and storage for this study will consist of digital files. Participant questionnaires will be completed and electronically managed using REDCap. After obtaining informed consent, participants will be assigned a de-identified code, and only this code will be used to identify participants within REDCap. A list linking participant codes and names will be stored separately from all other documents on a separate, password protected excel file located on a secure drive, to ensure participant confidentiality.

The neuroimaging data will be stored separately in a password-protected drive and access will be limited to individuals directly involved with the study. Only the de-identified code will be used to identify participants within the password-protected drive.

### 2.12. Data Analysis

To determine condition differences on the self-report clinical outcomes, a series of repeated measures analysis of variance (ANOVAs) will be used. A two (experimental group vs. TAU group) by two (Time 1 vs. Time 2) repeated measures ANOVA will be used to examine differences. Further, in order to determine if benefits are maintained long-term, a within-subject repeated measures ANOVA will be conducted for the experimental group across three testing times (Time 1, Time 2, Time 2). The primary outcome (STICSA) will be evaluated at α = 0.05. All other self-report measures are secondary, pre-specified a priori, and Bonferroni correction will be applied to account for multiple comparisons where appropriate. Given the proof-of-concept nature of the study, findings from secondary outcomes will be interpreted cautiously. Partial eta-squared (η^2^) will be reported for ANOVA effects, and Cohen’s d with 95% confidence intervals will be calculated to inform future sample size calculations. Analyses will follow an intent-to-treat (ITT) approach, with missing data handled using appropriate methods (e.g., multiple imputation where assumptions are met). All analyses will be performed with IBM SPSS Statistics 23 [93].

Preprocessing of fMRI data will be conducted using a combination of SPM12 (http://www.fil.ion.ucl.ac.uk/spm/software/spm12; accessed on 22 November 2025), FSL (https://fsl.fmrib.ox.ac.uk/fsl/fslwiki/; accessed on 22 November 2025), and custom MATLAB (version R2025b) scripts. Preprocessing will include motion correction, coregistration to the structural image, spatial normalization, nuisance regression (motion parameters and white matter/cerebrospinal fluid signals), and temporal band-pass filtering. ROI-to-ROI functional connectivity analysis will be performed using SPM to evaluate changes in connectivity within the DMN and SN. A priori-defined regions of interest (ROIs) for the DMN include the medial prefrontal cortex and posterior cingulate cortex, and for the SN include the anterior insula and dorsal anterior cingulate cortex. Growth curve analyses will be conducted within a linear mixed-effects modelling framework to assess changes in resting-state functional connectivity over time. A linear mixed-effects model will be used to examine both within-subject changes over time (Time 1 vs. Time 2) and between-group differences (experimental group vs. CAN-BIND healthy controls).

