### 2.2. Sample Size

In keeping with the minimum of 30 participants required to estimate a parameter in pilot and proof-of-concept trials [58,59], and based on prior studies applying neuroimaging to evaluate the impact of a mindfulness-based group intervention in non-perinatal anxiety and mood populations [37,38,60,61,62,63,64], a minimum of 20 participants will be randomized to each arm. Accounting for an estimated 20% attrition, we will recruit 50 participants total (25 per arm).

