Eligible and consenting participants will be randomly assigned to either the experimental (4-week mindfulness-based group intervention) or the TAU control group. Participants will be randomized using block randomization, with a 1:1 allocation ratio, using a computer-generated assignment sequence prepared prior to the study. Participants randomized to the mindfulness-based intervention group will complete a battery of self-report questionnaires post-treatment (Time 2) and 3 months post-treatment (Time 3). Questionnaires completed at Time 2 and Time 3 will be the same as those completed at baseline (Time 1) as part of the Green Prospective Database. Participants randomized to the TAU control group will complete the same battery of self-report questionnaires at Time 2. All questionnaires will be completed via Research Electronic Data Capture (REDCap). Participants randomized to the experimental group will also participate in an imaging session at the IRC at Time 1 and Time 2.

Participants randomized to the mindfulness-based intervention group will receive a $20 e-gift card for completing baseline questionnaires, post-treatment questionnaires, and another $20 after completing the 3-month follow-up questionnaires. They will also receive a $30 e-gift for participating in fMRI scans at baseline and post-treatment (for a total maximum of $120). Participants randomized to the TAU control group will receive a $20 e-gift card for completing baseline questionnaires and $20 after completing questionnaires following the 4-week TAU period (for a total maximum compensation of $40).

In addition to receiving financial compensation and the intervention being delivered entirely online, other attrition mitigation strategies have been put in place. Study staff will maintain regular contact via email and phone to remind participants about sessions and questionnaire-completion. Informal childcare support will be provided during MRI appointments, where a trained research assistant will be present while the participant completes the scan.

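### The primary STICSA test is a change-score comparison; adjusting Time 2 for the Time 1 score already collected would be more precise at no cost

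*Protocol article*

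**What the plan says.** Section 2.12 of the protocol article sets the between-arm analysis of the self-report measures: "A two (experimental group vs. TAU group) by two (Time 1 vs. Time 2) repeated measures ANOVA will be used to examine differences". The primary outcome is tested in that framework: "The primary outcome (STICSA) will be evaluated at α = 0.05". Section 2.8 restricts the instrument: "In the present study, only the trait scale of the STICSA will be used". No model with the Time 1 score as a covariate is mentioned for the self-report outcomes.

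On the analysis population, section 2.12 adds: "Analyses will follow an intent-to-treat (ITT) approach, with missing data handled using appropriate methods (e.g., multiple imputation where assumptions are met".

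On size, section 2.2 states that "a minimum of 20 participants will be randomized to each arm" and then: "Accounting for an estimated 20% attrition, we will recruit 50 participants total (25 per arm". The basis is a rule of thumb ("In keeping with the minimum of 30 participants required to estimate a parameter in pilot and proof-of-concept trials") together with earlier imaging studies. No power, effect size, SD or correlation between time points is given. Section 2.3 specifies block randomisation "with a 1:1 allocation ratio". Section 2.12 also intends Cohen's d with a confidence interval to help size a later trial.

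**The concern.** In a two-arm, two-time design, the group-by-time term of a repeated-measures ANOVA compares mean change between arms. Subtracting the whole Time 1 score fixes the slope of Time 2 on Time 1 at 1. In a randomised trial the natural slope is r when the SD is the same at both times. Using 1 instead of r adds noise, and more of it the lower r is. A baseline-adjusted model estimates the slope from the data and so uses the Time 1 score more efficiently.

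What is at stake is precision. The trial is small, its only declared primary outcome is this comparison, and its effect estimate is meant to inform the next sample size. The Time 1 score is collected from everyone anyway, so the precision given up costs nothing to recover.

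**Working it through.** **The plan's own figure.** 20 / (1 − 0.20) = 25 per arm, 50 in total. The stated size reproduces. Below, n = 20 per arm is the number expected with Time 2 data, and n = 25 is the number randomised.

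**Inputs.**
- From the article: two arms, 1:1 allocation, n = 20 or 25 per arm, α = 0.05. Two-sided testing is assumed, as an F test implies.
- Assumed, because the article gives no values: r from 0.3 to 0.8; a true difference of 0.5, 0.6 or 0.8 SD; the same SD (s) at both times and in both arms.

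**Step 1: what the ANOVA tests.** On one simulated data set with 20 per arm, the group-by-time F was 3.8018 and the squared two-sample t on change scores was 3.8018. They are the same test.

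**Step 2: variances of the arm difference.**
- Change score: 2(1 − r)s² × 2/n.
- Baseline-adjusted, slope known: (1 − r²)s² × 2/n.
- Ratio, adjusted to change: (1 + r)/2.
- Estimating the slope multiplies the adjusted variance on average by (2n − 3)/(2n − 4), which is 37/36 at n = 20.

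So at n = 20 the ratio is (1 + r)/2 × 37/36:
- r = 0.3: 0.65 × 37/36 = 0.67
- r = 0.5: 0.75 × 37/36 = 0.77
- r = 0.7: 0.85 × 37/36 = 0.87
- r = 0.8: 0.90 × 37/36 = 0.925 (about 0.93)

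The ratio reaches 1 when (1 + r)/2 = 36/37, that is r = 35/37 = 0.95. Above that, adjustment no longer gains.

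**Step 3: power.** Noncentral t, two-sided 0.05, with 2n − 2 degrees of freedom for the change score and 2n − 3 for the adjusted model, using the Step 2 variances including the slope factor. Each cell shows change score, then adjusted, at n = 20 per arm:

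| r | 0.5 SD | 0.6 SD | 0.8 SD |
|---|---|---|---|
| 0.3 | 26%, 36% | 35%, 48% | 55%, 72% |
| 0.5 | 34%, 42% | 46%, 56% | 69%, 80% |
| 0.7 | 51%, 57% | 67%, 72% | 89%, 93% |
| 0.8 | 68%, 72% | 83%, 86% | 97%, 98% |

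If all 25 per arm contributed complete data, the gap would remain. At 0.6 SD and r = 0.5, power is 55% against 66% (slope factor 47/46).

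**Step 4: in participants.** To match the adjusted analysis with 20 per arm, the change-score test would need 20 divided by the ratio: 29.9 per arm at r = 0.3, 25.9 at 0.5, 22.9 at 0.7 and 21.6 at 0.8.

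**Step 5: validity.** In 4,000 simulated trials per setting with no true effect (n = 20 per arm; r = 0.3, 0.5, 0.7), rejection rates were 4.6% to 5.2% for the change score and 4.5% to 5.4% for the adjusted model. Both hold the nominal 5%.

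**The case against.** The strongest reply is that this is a choice between two valid tests. Under randomisation the change-score estimate is unbiased, and chance baseline imbalance is already counted in its variance. The article makes no power claim, so no stated target is missed. The outcome is a trait scale, for which a high four-week correlation is plausible, and at r = 0.8 the gain at 0.6 SD is only about three percentage points. All of this stands. It limits the point to efficiency and makes its size depend on r, but it gives no reason to prefer the less precise test.

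Two stronger readings are tempting and are not supported.

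- **That the ANOVA uses only participants with both measurements and so fails intention-to-treat.** Run on observed data, it would be a complete-case analysis. But section 2.12 sets no such restriction, commits to intention-to-treat and names multiple imputation. An ANOVA on imputed data can include everyone randomised, and an ANCOVA on observed data would lose the same people. The attendance condition for the primary analysis in section 2.5 is a separate question about who is analysed; it does not follow from the choice of model.
- **That the primary test is undefined because the ANOVA effect is not named.** Group-by-time is the usual reading of a pre/post two-arm design, and naming the term is a detail commonly left to an analysis plan, which is not shown here.

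**Conclusion.** The point holds as one of efficiency. Section 2.12 fixes a valid primary test that is less precise than a baseline-adjusted comparison unless the Time 1 to Time 2 correlation is about 0.95 or more. Over assumed r of 0.3 to 0.8 with 20 per arm, adjustment lowers the variance by about 33% to 7%. At an assumed 0.6 SD, it adds about 13 percentage points of power at r = 0.3 and about 3 at r = 0.8. The benefit is clear at r of 0.3 to 0.5 and modest at 0.7 to 0.8.

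These figures rest on an assumed r and effect size, equal SDs at both times and in both arms, and a two-sided test. The change is worth making because it is free and the estimate is meant to size a later trial. It does not correct an invalid analysis.

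**What to change.** In section 2.12, replace the 2 × 2 ANOVA for the between-arm comparison with the Time 2 STICSA difference between arms adjusted for Time 1 STICSA, in all randomised participants. Either of two forms would do:

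- ANCOVA, using the multiple imputation that the section already names; or
- a mixed model for Time 1 and Time 2 with a common baseline mean in both arms, which uses everyone with any data.

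Report the adjusted mean difference with its 95% CI as the primary result, and use the same model for the secondary scales. Cohen's d can still be derived for sizing the later trial.

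The cost is wording only: no added data, visits or participants. Section 2.12 already plans mixed models for the imaging data. The change should be made before any outcome data are examined by arm.

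### The three-time within-subject F test cannot show whether benefits are maintained, even after the evident Time 2/Time 3 slip is corrected

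*Protocol article*

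**What the plan says.** Section 2.12 gives the follow-up analysis a purpose, "in order to determine if benefits are maintained long-term", and a method: "a within-subject repeated measures ANOVA will be conducted for the experimental group across three testing times (Time 1, Time 2, Time 2"). Time 3 is not named anywhere in that section. It is defined in section 2.3, where the mindfulness arm completes the battery "post-treatment (Time 2) and 3 months post-treatment (Time 3").

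For the other arm, section 2.3 says: "Participants randomized to the TAU control group will complete the same battery of self-report questionnaires at Time 2". No later assessment is described for TAU, and section 2.5 offers those participants the intervention once their 4 weeks are over.

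On testing, section 2.12 says "The primary outcome (STICSA) will be evaluated at α = 0.05". It adds a general Bonferroni correction for the secondary measures and promises Cohen's d with 95% confidence intervals for planning later trials. Neither statement is tied to a Time 3 comparison.

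**The concern.** The list of time points is wrong as printed, and this is the only sentence that says how the 3-month data will be analysed.

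Correcting the label does not make the test suit its purpose. The null hypothesis of a one-group, three-level repeated-measures ANOVA is that all three means are equal. An improvement between Time 1 and Time 2 violates that null whatever happens afterwards. A significant result therefore fits lasting benefit, partial loss and complete return to baseline alike.

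At stake is the durability statement. Section 3 expects this trial to provide the basis for a larger one, so a durability signal that rests on the wrong test could carry forward into its design.

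**Working it through.** **Inputs from the protocol article**
- Sample size (section 2.2): "a minimum of 20 participants will be randomized to each arm" and "Accounting for an estimated 20% attrition, we will recruit 50 participants total (25 per arm").
- Allocation (section 2.3): "with a 1:1 allocation ratio".
- Alpha 0.05 (section 2.12).

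**Assumed inputs, because the article gives none**
- Time 1 to Time 2 improvement d of 0.3, 0.5 or 0.8 SD.
- Equal SDs at all times.
- Within-person correlation ρ of 0.5 or 0.7, plus three patterns that decay with time.

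**Step 1: the plan's own figure.** 20 / (1 − 0.20) = 25 per arm, and 2 × 25 = 50. This reproduces and is not in dispute. It suggests 20 completers in the mindfulness arm, or 25 with no attrition.

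**Step 2: two opposite outcomes, with Time 3 restored.** Write the means relative to baseline.
- Full maintenance (0, −d, −d): the grand mean is −2d/3 and the deviations are 2d/3, −d/3, −d/3. The sum of squares is (4 + 1 + 1)d²/9 = (2/3)d².
- Complete relapse (0, −d, 0): the grand mean is −d/3 and the deviations are d/3, −2d/3, d/3. The sum of squares is (1 + 4 + 1)d²/9 = (2/3)d².

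**Step 3: probability of a significant F.** Under compound symmetry the noncentrality is λ = n × (sum of squares) / (1 − ρ) in SD units, with 2 and 2(n − 1) degrees of freedom. For n = 20, d = 0.5, ρ = 0.5: λ = 20 × (2/3) × 0.25 / 0.5 = 6.67 under either outcome.

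| n | ρ | d | λ | Maintenance | Relapse |
|---|---|---|---|---|---|
| 20 | 0.5 | 0.3 | 2.40 | 0.246 | 0.246 |
| 20 | 0.5 | 0.5 | 6.67 | 0.596 | 0.596 |
| 20 | 0.5 | 0.8 | 17.07 | 0.954 | 0.954 |
| 20 | 0.7 | 0.5 | 11.11 | 0.826 | 0.826 |
| 25 | 0.5 | 0.5 | 8.33 | 0.707 | 0.707 |
| 25 | 0.7 | 0.5 | 13.89 | 0.909 | 0.909 |

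The power values depend on the assumptions. Their equality does not depend on n, d or ρ.

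**Step 4: relaxing compound symmetry.** Simulated with 20,000 runs per cell, n = 20, d = 0.5, Greenhouse–Geisser corrected:

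| Correlations T1–T2 / T2–T3 / T1–T3 | Maintenance | Relapse |
|---|---|---|
| 0.7 / 0.7 / 0.49 | 0.676 | 0.751 |
| 0.7 / 0.55 / 0.45 | 0.627 | 0.659 |
| 0.8 / 0.5 / 0.4 | 0.615 | 0.643 |

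Equality no longer holds, but it fails in the unhelpful direction. Unequal SDs over time were not examined.

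**Step 5: what targeted contrasts do.** Paired comparisons, d = 0.5, two-sided 0.05, compound symmetry, proportion significant:

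| n | ρ | Contrast | Maintenance | Relapse |
|---|---|---|---|---|
| 20 | 0.5 | Time 3 − Time 1 | 0.57 | 0.05 |
| 20 | 0.5 | Time 3 − Time 2 | 0.05 | 0.56 |
| 25 | 0.5 | Time 3 − Time 1 | 0.67 | 0.05 |
| 20 | 0.7 | Time 3 − Time 1 | 0.78 | 0.05 |
| 25 | 0.7 | Time 3 − Time 1 | 0.87 | 0.05 |

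**Step 6: precision of the loss-of-benefit contrast.** The 95% half-width is t × √(2(1 − ρ)) / √n. For n = 20 and ρ = 0.6: 2.093 × 0.894 / 4.472 = 0.42 SD. It is 0.47 SD at ρ = 0.5 and 0.36 SD at ρ = 0.7.

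**The case against.** The strongest reply is that a three-level ANOVA is conventionally followed by pairwise comparisons. The article mentions Bonferroni correction and Cohen's d with intervals, it nowhere says that a significant F alone will be read as maintenance, and a condensed article may leave named contrasts to the full protocol or SAP. Part of this stands: a reader should not infer that the sponsor will claim durability from the F test alone, or that no contrasts are planned. But the point is not missing detail. The article states a question and a test, and the test does not address the question. Nothing shown ties the answer to a Time 3 contrast.

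Three stronger readings are tempting and not supported.

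- *The 3-month data will not be analysed.* The abstract lists a 3-month follow-up, section 2.3 defines Time 3, section 2.7 counts three questionnaire time points for this arm, and the sentence itself speaks of three times. The duplicate is a slip.
- *The absence of TAU data at Time 3 is a hidden flaw.* It is openly described. Because TAU participants may take up the intervention after 4 weeks, a later assessment would not give a clean untreated comparison. The analysis is labelled as within the experimental group. It limits interpretation only.
- *The trial's main result is compromised.* The randomised comparison is the separate two-by-two analysis of Time 1 and Time 2.

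**Conclusion.** The concern holds at moderate severity. The printed time points need correction. With Time 3 restored, the omnibus F test still cannot distinguish full maintenance from complete relapse: equality is exact under compound symmetry and equal SDs, and in the three decaying-correlation patterns tried relapse was favoured by about 3 to 8 percentage points. The individual probabilities rest on effect sizes and correlations that the article does not give. Other variance patterns could shift the balance either way, but they would not turn a test of any difference into a test of maintenance.

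**What to change.** In section 2.12, change the time points to Time 1, Time 2, Time 3. Then state that any maintenance claim rests on two prespecified STICSA contrasts with 95% confidence intervals, and not on the omnibus F:

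- Time 3 minus Time 1, the net change still present at 3 months;
- Time 3 minus Time 2, the loss of benefit since the end of treatment.

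Both can come from the planned repeated-measures model with the intent-to-treat and imputation approach already stated; a mixed model is optional. Add that the 3-month result is an uncontrolled within-arm change, since TAU has no assessment then, and is not attributed to the intervention.

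The cost is a wording change with no new data and a narrower follow-up claim. The Time 3 minus Time 2 interval will be wide, so the text should also say that a non-significant difference there is not proof of maintenance.

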### 1.5. Current Study

Given the physical and psychological components of ADs and the promising effects of mindfulness intervention on anxiety, emotion regulation, and interoception in non-postpartum populations, we developed a mindfulness protocol for postpartum mothers/BPs with ADs. This proof-of-concept randomized controlled trial will examine the effects of a 4-week mindfulness-based group intervention compared to treatment as usual (TAU). The primary aim is to evaluate the intervention’s impact on AD symptoms using both subjective (self-reported anxiety, emotion regulation, and interoception) and objective (functional connectivity of brain networks associated with these processes) measures. We hypothesize that participants will show reductions in anxiety and improvements in emotion regulation and interoception. We also expect to observe changes in functional connectivity in relevant brain networks (e.g., the DMN and SN). To our knowledge, this will be the first study to assess the efficacy of a mindfulness protocol for postpartum mothers/BPs with ADs using a combination of self-report and neuroimaging outcomes.

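### Emotion regulation and interoception are named in the primary aim but tested only as secondary outcomes under Bonferroni, which Holm improves on at no cost

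*Protocol article*

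**What the plan says.** Section 1.5 gives the primary aim as the intervention's "impact on AD symptoms using both subjective (self-reported anxiety, emotion regulation, and interoception) and objective" measures, and hypothesises that "participants will show reductions in anxiety and improvements in emotion regulation and interoception". The three self-report constructs stand there on an equal footing.

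Section 2.8 lists one primary outcome, the trait scale of the STICSA. Section 2.12 agrees: "The primary outcome (STICSA) will be evaluated at α = 0.05". It then adds "All other self-report measures are secondary, pre-specified a priori", and says that "Bonferroni correction will be applied to account for multiple comparisons where appropriate".

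Section 2.9 lists 12 secondary instruments: GAD-7, PSWQ, DERS, MAIA-2, ISAQ, FFMQ-SF, EPDS, PSS, SPS, PBQ, DAS and WHOQoL. Emotion regulation is measured by one of them ("The DERS is a 36-item self-report scale designed to assess difficulties with emotion regulation") and interoception by two, MAIA-2 and ISAQ.

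Section 2.12 also says that secondary findings will be read with caution, and that Cohen's d with 95% confidence intervals will be reported to help size a later trial.

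**The concern.** A reader of section 1.5 would expect emotion regulation and interoception to have primary status. A reader of sections 2.8 and 2.12 would find them tested beside social support, bonding and relationship adjustment. When the trial reports, the same DERS result could be presented as answering the primary aim or as one corrected secondary among 12, and the document supports both presentations.

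The second issue is the choice of correction. With about 20 analysable participants per arm, any avoidable loss of power on the secondary scales matters. Single-step Bonferroni loses some power for no gain in error control, because Holm's step-down version gives the same guarantee.

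**Working it through.** **1. Sample size.** Section 2.2 asks for at least 20 per arm and allows 20% attrition. 40 / (1 − 0.20) = 50, or 25 per arm, which reproduces the stated total. The plan states no power.

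**2. Aim against hierarchy.**

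| Construct | Section 1.5 | Sections 2.8, 2.9 and 2.12 |
|---|---|---|
| Anxiety | primary aim | STICSA primary, α = 0.05; GAD-7 and PSWQ secondary |
| Emotion regulation | primary aim | DERS, secondary |
| Interoception | primary aim | MAIA-2 and ISAQ, both secondary |

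Two of the three self-report constructs in the primary aim, measured by 3 of the 12 secondary instruments, have no primary test.

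**3. Why Holm dominates.** Take 12 tests with ordered p-values p(1) ≤ … ≤ p(12).
- Bonferroni rejects every p ≤ 0.05/12 = 0.00417.
- Holm compares p(j) with 0.05/(13 − j) and stops at the first failure. The thresholds are 0.05/12 = 0.00417, 0.05/11 = 0.00455, and so on up to 0.05.
- If p(j) ≤ 0.05/12, then p(j) and all smaller p-values pass their Holm thresholds, since 0.05/(13 − j) ≥ 0.05/12. So every Bonferroni rejection is also a Holm rejection.
- Both hold the familywise error at 0.05 or less under any correlation between the scales.

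**4. Power for one scale at 0.05/12.** The group-by-time test in a 2 × 2 repeated measures ANOVA is a t test on change scores. With d on the raw-score scale and pre-post correlation ρ, the effective size is d / √(2(1 − ρ)). The non-centrality is that value × √(n/2), on 2n − 2 degrees of freedom. At n = 20, √(n/2) = 3.162 and the degrees of freedom are 38. The document gives neither d nor ρ for this trial, so both are assumptions. The value 0.74 is the DERS test-retest reliability in section 2.9, the only related figure.

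| d | ρ | Effective d | Power at 0.05 | Power at 0.05/12 |
|---|---|---|---|---|
| 0.5 | 0.5 | 0.50 | 34% | 9% |
| 0.8 | 0.5 | 0.80 | 69% | 32% |
| 0.5 | 0.74 | 0.5 / 0.721 = 0.69 | 57% | 22% |
| 0.8 | 0.74 | 0.8 / 0.721 = 1.11 | 93% | 68% |

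**5. Gain from Holm.** Simulation of 12 scales with 20 per arm, correlation 0.5 between scales, ρ = 0.5 and 20,000 runs. The figures are average power over the scales with a real effect.

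| d | Scales with a real effect | Bonferroni | Holm |
|---|---|---|---|
| 0.8 | 6 of 12 | 32% | 35% |
| 0.8 | 12 of 12 | 32% | 41% |
| 0.5 | 6 of 12 | 8.6% | 9.2% |
| 0.5 | 12 of 12 | 8.6% | 10.4% |

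With no real effects, both methods made at least one false rejection in 3.8% of runs, within the 5% limit.

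**The case against.** **Proof of concept.** The trial claims no power, names one primary outcome, promises caution on the rest and plans effect sizes with intervals. A broad aim served by one primary outcome is common, and the Discussion describes the intervention's main intention as reducing anxiety and fostering mindfulness. This stands as a reason to keep the point modest. It does not remove the mismatch, because section 1.5 still calls the wider set the primary aim and section 2.12 still plans corrected significance tests.

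**Bonferroni is valid.** True, and it gives simple matching simultaneous intervals, which Holm does not. That advantage is not used here, because the plan mentions only 95% intervals for Cohen's d and no Bonferroni-adjusted ones.

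**Stronger readings that the documents do not support.**
- *A fixed strict threshold.* A reader might infer that DERS, MAIA-2 and ISAQ are certain to be tested at 0.0042 or below. Section 2.12 states no divisor; a family of three would give 0.05/3 = 0.0167. The exact family is detail that an analysis plan not shown here may supply, so its absence alone is no finding.
- *Testing every subscale.* Section 2.9 describes subscales as background on the instruments, for example "The MAIA-2 has 8 subscales assessing dimension of noticing". Nothing says they will be tested, so a larger divisor built from them is speculation. The same holds for an interoception claim drawn from any single subscale. The direction of benefit on the ISAQ is likewise analysis-plan detail.
- *Little chance of a clear answer.* This depends on the assumptions: at 0.05/12, power runs from 9% to 68% in the table above. Nor is Bonferroni the only cause, since at d = 0.5 and ρ = 0.5 power is 34% with no correction at all.
- *A fixed testing order.* Testing STICSA, then DERS, then MAIA-2, each at 0.05, looks attractive. But each later test depends on the earlier ones succeeding, which can leave MAIA-2 with less power than Bonferroni does. It is a debatable trade-off, not a correction.

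**Conclusion.** The point holds in a limited form. The primary aim in section 1.5 is wider than the primary outcome in sections 2.8 and 2.12, and the document should be made consistent. Bonferroni is also a dominated choice: that Holm never rejects less at the same familywise error is exact and rests on no assumption.

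The size of the gain does rest on assumptions: 20 per arm, 12 tests, and correlations of 0.5 between scales and between time points. On these it is about 3 to 9 points of average power at d = 0.8, and about 2 points at d = 0.5 if all effects are real. Holm will not turn a small trial into a well-powered one. It is worth adopting because it costs nothing.

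**What to change.** - **Section 2.12:** replace Bonferroni with Holm's step-down procedure at familywise 0.05, applied to the 12 secondary scales in section 2.9 as one fixed family. Drop the qualifier that makes the correction conditional. The STICSA stays outside the family at 0.05.
- **Section 1.5:** restate the primary aim as the effect on anxiety measured by the STICSA, and name emotion regulation (DERS) and interoception (MAIA-2, ISAQ) as secondary aims. The hypotheses can stay, labelled to match.

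The cost is a change of wording, made before any Time 2 data are seen. It needs no extra participants, visits or measures. Holm gives up simple matching simultaneous intervals, but the plan does not call for them, and the planned 95% intervals for Cohen's d are unaffected.
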